### Study stage 1: optimising and validating pharmacological interventions

The aim of the preliminary stage of the study is to define and validate (technically and pharmacologically) safe methods to create reliably and reproducibly three different patterns of plasma cortisol. These patterns were based on the combinatory administration of metyrapone and hydrocortisone. Metyrapone was chosen to suppress endogenous cortisol production for both safety reasons (as it has a short half-life [17]) and because it does not interfere with cortisol’s molecular physiology. Metyrapone blocks cortisol synthesis by inhibiting steroid 11β-hydroxylase [18]. These three methods for creating different patterns of systemic cortisol dynamics in healthy individuals offered the basis for the temporal design of study stage 2 (see below).

Five healthy volunteers participate in stage 1. After giving written consent, they undergo a five-day treatment scheme, where metyrapone per os (on a full stomach to minimise gastric side effects) treatment is gradually increased from 0.5 g on day 1 to 2.5 g on day 4 (see Table 2). Hydrocortisone replacement is achieved in one of three modes: (i) either orally to mimic the current therapeutic protocols for glucocorticoid replacement or via a subcutaneous pump, delivered (ii) continuously or (iii) in pulses. The total daily dose of hydrocortisone is: 20 mg (per os), 19.8 mg (continuous with varying rhythm throughout the day) [19], 19.9 mg (pulsatile: eight times/day being a close approximation of the adrenal glucocorticoid natural ultradian pattern of secretion) (see Table 3). For technical reasons, hydrocortisone delivery via the pumps differs very slightly from the oral 20 mg dose. We have chosen to deliver slightly less by subcutaneous infusion to compensate for the slightly higher blood levels achieved using this route [20, 21]. Recently, our group has published the technical data (dose range and frequency of individual pulses estimation) and the functional validation of the pulsatile pump [22].

**Table 2 Tab2:**

Outline of the five-day metyrapone treatment scheme during study stage 1

Medication was received orally (pills of 250 mg of metyrapone). The doses in blue letters have been administered during the 24-hour blood sampling study

^a^For the purposes of the optimisation procedure, various doses were tested in different subjects at particular time points during the five-day treatment scheme to secure effective adrenal gland suppression (see Fig. 4)

^b^The last dose of the day was shifted from, initially, dinner time to just before going to sleep to ensure effective adrenal gland suppression during sleep (see Fig. 4). Participants are strongly advised to take metyrapone with a glass of milk or a snack to avoid any gastric discomfort

**Table 3 Tab3:** Outline of the three different modes of hydrocortisone replacement in healthy individuals under metyrapone administration

Time of day	Per os	SC continuous	SC pulsatile
00:00		0.1 mg/hour	0.5 mg
01:00			
02:00		2 mg/hour	
03:00			4 mg
04:00			
05:00			
06:00			4 mg
07:00	After waking up (10 mg)		
08:00		1 mg/hour	
09:00			4 mg
10:00			
11:00			
12:00		0.4 mg/hour	2.3 mg
13:00	During lunch (5 mg)		
14:00			
15:00			2.3 mg
16:00			
17:00			
18:00			2.3 mg
19:00	During dinner (5 mg)		
20:00		0.1 mg/hour	
21:00			0.5 mg
22:00			
23:00			

The last two modes involve the subcutaneous (SC) delivery of hydrocortisone via a pump; the continuous pump (Animas® Vibe™ Insulin Pump) is programmed to constantly deliver hydrocortisone but with a changing flow rate throughout the day. The pulsatile pump (Crono P®, CANE Applied Medical Technology Ltd, Cambridge, UK) is programmed to deliver a certain amount of hydrocortisone every three hours with a rhythm of 10 μL/s [22]

All visits take place in the Joint Clinical Research unit (UHB). On day 1 participants are fitted with the subcutaneous pump and are given precise instruction on how to receive their oral medication. On day 3 participants wearing either of the pumps attend the unit for a pump syringe and line change. On day 5, the 24-hour blood sampling study is undertaken, using the human automated blood sampler (HABS). Blood samples are collected via an intravenous cannula every one hour for serum corticotrophin (ACTH) and cortisol concentration estimation. For those receiving hydrocortisone via the subcutaneous pulsatile pump, cortisol was being estimated every 10 minutes, since we anticipated that cortisol would fluctuate in a more dynamic manner (approximating its normal, ultradian rhythm). During the 24-hour sampling procedure, participants give approximately half a pint of blood (half the amount of blood taken at blood donation). All blood is replaced with an equal volume of normal saline.

During the blood sampling period, participants are served a hot meal at 7:00 pm, breakfast at 07:00 am and lunch at 12:30 pm. Refreshments are offered between meal times and recorded. Participants are asked to go to sleep at 11:00 pm when the lights are switched off. During the lights-on period, participants are allowed to work, read, watch films or relax. A member of staff is present in a room adjacent to the experimental room to monitor them at all times. At the end of the study (in the early afternoon), when the intervention is terminated, participants are instructed to take orally 5 mg of hydrocortisone during dinner to ensure proper cortisol replacement for that day. This ensures there has been adequate time for the metyrapone to have cleared and resumption of endogenous cortisol production. Participants are called the following day to check that there have been no adverse events and note any issues they wish to report.

Cortisol samples were allowed to clot at room temperature prior to centrifugation and serum was frozen at −80 °C until assayed. Samples for ACTH were collected in chilled ethylenediaminetetraacetic acid-containing tubes and kept on ice until centrifugation at 4 °C within 30 minutes. Plasma was stored at −80 °C until assayed. Analysis is performed by the department of clinical biochemistry at the UHB using an electrochemiluminescence immunoassay (Cobas®, Roche). Cross-reactivity with 11-deoxycortisol was 4.1 %. This immunoassay has an intra-assay coefficient of variation ranging from 1.5 % to 6.1 % on sample concentrations of 0.170 μg/dL to 0.718 μg/dL http://www.accessdata.fda.gov/cdrh_docs/reviews/K043175.pdf.

### Study stage 2: randomisation and blinding

The second stage of the study is the randomised, double-blinded, placebo-controlled, three-way crossover investigation, where participants undergo all three optimised five-day treatment schemes as finalised in the previous stage. Randomisation schedules were generated using IBM SPSS® v19 software by staff members not directly involved in data collection for this study. Dispensing and processing of all medication/placebo is managed by Bristol Royal Infirmary University Hospital Pharmacy, ensuring that study researchers remain blinded to the conditions. To ensure that the study remains double-blind, all participants are required to take the same daily regime of tablets and remain connected to a subcutaneous pump (continuous or pulsatile). Each week one of these treatments will be placebo (either placebo tablets or 0.9 % saline infusion via the pump). In addition, the study investigators responsible for care of the pumps have no input into the psychological testing. There is a minimum of two weeks between each of the three study arms. Participants and study researchers are therefore unaware of the order of the arms of their hydrocortisone replacement.

On day 1 of each arm, participants are connected to the pump via a line that is inserted into the subcutaneous tissue of the abdomen and are trained to handle the pump by themselves (detach-reattach). Participants are given metyrapone and identically encapsulated tablets containing either hydrocortisone or placebo and the investigator explains to them the five-day treatment plan they will follow. The participants receive instructions in cases of an emergency (hypoadrenal symptoms). Finally, they also receive their study android phone that monitors their everyday state of mood and reactivity at random points within each day (see below). Participants also give a urine sample to be tested for the presence of drugs of abuse.

On day 3 participants attend the hospital for a pump syringe and pump line change, while the investigator also monitors individuals’ compliance to the treatment scheme (counting the number of remaining pills) and to answering the study phone’s questions. Finally, on day 5 participants attend CRICBristol where they undergo MRI scanning, complete a sleep questionnaire and undertake a series of behavioural tests (see below). At the end of the study visit, participants return all study material (android phone, remaining pills), are disconnected from the pump and are instructed to take 5 mg of hydrocortisone orally during lunch and again during dinner to ensure proper cortisol replacement for the remaining day. This ensures there has been adequate time for the metyrapone to have cleared and resumption of endogenous cortisol production. They will then receive a follow-up phone call the following day to check to see how they are feeling and if they have any issues they wish to report.

Compliance to the treatment protocol is encouraged by (1) giving participants at arm day 1 a detailed, written five-day timetable, with instructions on the timings and the number of metyrapone and hydrocortisone/placebo pills they need to take, (2) counting the remaining pills at arm days 3 and 5 to verify that they are consumed in the proper quantity, and (3) prompting the participants at arm day 3 to accurately follow their treatment scheme and to constantly wear the pump. Furthermore, compliance to the oral treatment protocol is also supported via three reminder messages (in the morning, at 1:00 pm and at 7:00 pm) delivered every day through the study phones carried by each subject.

### Assessments during study stage 2

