Volunteers are free to withdraw from the study at any time. Should a subject withdraw from the study, another will be recruited in his/her place. It is not anticipated that withdrawn volunteers will require any follow-up.

With regards to a randomisation and/or blinding code break during the second stage of the study, a copy of the codes will be kept in the Bristol Royal Infirmary University Hospital Pharmacy and in the site file. The codes may only be broken under the following conditions with the agreement of the chief investigator and REC except under the case of an emergency: (i) it is deemed clinically necessary (for example, treatment of an adverse event is dependent upon knowledge of the drug administered), (ii) the study must be terminated for safety reasons, or (iii) a third party requires the information (for example, a coroner).

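### The double-blind claim covers the route of hydrocortisone, not pulsatile versus continuous delivery: the pump worn rules out one subcutaneous regimen in every arm

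*Protocol article*

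**What the plan says.** The section Study stage 2: randomisation and blinding makes the claim: "The second stage of the study is the randomised, double-blinded, placebo-controlled, three-way crossover investigation". It gives the means as well. Tablets are the same in every arm and one pump is worn: "all participants are required to take the same daily regime of tablets and remain connected to a subcutaneous pump (continuous or pulsatile"). The dummy is then defined: "Each week one of these treatments will be placebo (either placebo tablets or 0.9 % saline infusion via the pump"). From this, a minimum two-week gap and the exclusion of pump carers from psychological testing, it concludes: "Participants and study researchers are therefore unaware of the order of the arms of their hydrocortisone replacement".

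The footnote to Table 3 describes the two pumps. For one scheme, "the continuous pump (Animas® Vibe™ Insulin Pump) is programmed to constantly deliver hydrocortisone but with a changing flow rate throughout the day". For the other, "The pulsatile pump (Crono P®, CANE Applied Medical Technology Ltd, Cambridge, UK) is programmed to deliver a certain amount of hydrocortisone every three hours".

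The stage 2 section says that the schemes are those finalised in stage 1, and the Fig. 2 legend says the same of the interventions. Participants are trained on day 1 of each arm to detach and reattach the pump. Under Data analysis for study stage 2, the primary outcome is the area under the curve of tiredness and mood from ecological momentary assessment (EMA). The EMA section calls that assessment subjective.

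**The concern.** The masking has one dummy for two distinctions. Capsules against infusion is covered, because one of them is always placebo. Pulsatile against continuous is not: only one pump is worn, each scheme has its own make and delivery pattern, and the article describes no second dummy pump, common device or concealment.

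The uncovered distinction is the central one. Main research questions and hypothesis sets delivery with the ultradian rhythm against a constant infusion that abolishes it. The primary outcome for that contrast is the participant's own rating of tiredness and mood, given while he wears the device. Keeping pump carers away from the tests protects the testers, not a self-rating. An expectation about one kind of pump could therefore produce or mask a difference, and the report would still describe it as double-blind.

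**Working it through.** The plan gives no figure for blinding to reproduce, and its sample-size statement is not affected. The check lists what the device reveals.

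**Inputs from the article.** Three regimens per participant: oral (O), continuous (C) and pulsatile (P). One pump per arm. C uses the continuous model and P the pulsatile model (Table 3 footnote).

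**Assumptions.** Stage 2 uses the same two models. The wearer can tell them apart and knows which scheme each serves. The six orders are equally likely. The oral arm's pump is not stated, so let q be the probability that it is the pulsatile model.

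**Step 1: pulsatile versus continuous.** P(regimen C | pulsatile model worn) = 0 and P(regimen P | continuous model worn) = 0, for every q. One subcutaneous regimen is excluded in each arm.

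**Step 2: naming the exact regimen in one arm.** Without device information the chance is 1/3. With it:

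- P(C | continuous model) = (1/3) / [1/3 + (1 − q)/3] = 1/(2 − q)
- P(P | pulsatile model) = (1/3) / [1/3 + q/3] = 1/(1 + q)

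| Oral arm's dummy | P(C given continuous model) | P(P given pulsatile model) |
|---|---|---|
| Always continuous (q = 0) | 1/2 | 1 |
| Split 50:50 (q = 1/2) | 2/3 | 2/3 |
| Always pulsatile (q = 1) | 1 | 1/2 |

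With a fixed dummy, the other model identifies its arm from day 1 to anyone who knows the rule. Averaged over arms the chance is still 2/3, for example (1/3 × 1) + (2/3 × 1/2) = 2/3 at q = 0. Balancing therefore removes certainty, not the average gain.

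**Step 3: is the pump active?** Two of the three arms have an active pump, so the chance is 2/3 before any device is seen. At q = 1/2 it is still 2/3 afterwards. In a single arm the device then says nothing about oral versus subcutaneous.

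**Step 4: after all three arms.** The oral arm repeats one of the two models, so one model is worn twice and the other once. The model worn once cannot be the dummy, so that arm had an active pump. The other two arms are one active and one oral, in either order. The full order is guessed correctly with probability 1/2, against 1/6 for six equally likely orders. This holds for every q.

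**Step 5: timing.** The model worn once falls in arm 1, 2 or 3 with probability 1/3 each. Unless a fixed dummy is known, that arm is still running when the deduction becomes possible only if it is the third. Otherwise its EMA data are already complete.

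**The case against.** The strongest reply is that seeing a device is not knowing the treatment. With identical capsules and a saline pump in the oral arm, a man wearing either pump may still be on oral hydrocortisone. The article is also a condensed account: pump makes are named in the Table 3 footnote and the stage 1 figure legends, not in the stage 2 section, and a dummy-pump schedule is the kind of detail left to a full protocol. The study is a physiological pilot with less expectation-prone outcomes, namely startle electromyography and imaging.

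Much of this stands. A reader might infer that the trial is effectively open-label, or that two of three arms are known to the participant. The article does not support that: the device excludes one regimen of three, and the certain deduction usually comes too late to affect the arm it concerns. A reader might also take the 2/3 as the chance of correctly believing the pump active, raised from 1/3. It is not; that chance is 2/3 with or without the device.

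Two further inferences fail. That "a copy of the codes will be kept in the Bristol Royal Infirmary University Hospital Pharmacy and in the site file" does not show that the blind is open, because the same section limits code breaks to three conditions, with agreement required except in an emergency. Nor does the term placebo-controlled mislead, since the stage 2 section says what the placebo is.

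The reply does not rescue the conclusion drawn in the stage 2 section. The article sets out its masking and infers unawareness from it. For pulsatile versus continuous, that inference does not follow from the measures listed.

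**Conclusion.** The blinding statement is wrong as written for one contrast. The masking conceals the route of hydrocortisone in part; it does not conceal which kind of pump is worn. Pulsatile versus continuous, the ultradian contrast, is therefore not device-blind on the self-rated EMA primary outcome.

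The size depends on the unstated oral-arm pump. With a 50:50 split, the exact regimen in one arm can be named with probability 2/3 instead of 1/3. With one fixed dummy model, the other model reveals its arm from day 1. Under either rule, the full order can be guessed afterwards with probability 1/2 instead of 1/6. These figures rest on the same models being used in stage 2 and on participants understanding what each one does. A participant who does not understand can still tell the two pump conditions apart. How much expectation would shift EMA scores cannot be derived from the article.

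**What to change.** 1. If one pump model can run both profiles, use it in all arms. If not, restate in the stage 2 section that the trial is double-dummy blinded for route only and that pulsatile versus continuous is not participant-blind to device. Interpret the EMA result for that contrast alongside the startle and imaging outcomes.

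2. State which pump is worn in the oral arm, and have the pharmacy schedule balance the two models across participants so that neither identifies its arm on day 1. With 15 participants the nearest split is 8 and 7, which moves the 2/3 only to 1/(1 + 8/15) = 15/23 = 0.65 or 1/(1 + 7/15) = 15/22 = 0.68. Recruitment was under way at submission, so this can apply only to those not yet allocated. It does not restore the blind between the two pump regimens.

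3. Optionally record each participant's treatment guess, preferably once after the last arm so that the question does not prompt guessing in later arms. Report it descriptively only: 15 men are too few to analyse by guess, and the drug's own effect on mood can drive the guess.

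The cost is a change of wording, a pharmacy rule and at most one question. The downside is a weaker but accurate blinding claim.

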#### Ecological momentary assessment

This is a subjective test that relies on the repeated, five-day long collection of real-time data on subjects’ behaviour/emotional status in the subjects’ natural environment. For this purpose, volunteers are asked to continuously carry a modified android mobile phone, for the whole duration of each of the three five-day study periods. This is appropriately programmed to ask some questions contained in the Identity-Consequence Fatigue Scale [23] and visual analogue scale [24] concerning the subjects’ state of reactivity and feeling of well-being. Time-based sampling is applied; assessments are solicited based on a time schedule, but at random time intervals. Additionally the phone reminds the holder to take his oral study medication. Moreover, the device asks the subject to complete a morning (available until around 10:00 am) and an evening report (available at 07:00 pm onwards) each study day. Anonymised data (subjects’ feedback), both quantitative and qualitative, are stored in the android phone, and are transferred to University of Bristol computers.

Ecological momentary assessment (EMA) techniques (versus static retrospective self-reports of behaviour) take into consideration the dynamic changes in behaviour over time and across situations and under a real-world setting. Moreover, they avoid relying on individuals’ autobiographical memory (which is the case in retrospective self-reports), which is prone to random error but also fraught with systematic bias [25]. Evidence from other clinical studies, such as smoking cessation, indicates that ambulatory monitoring of subjective states provides greater temporal resolution than can be achieved by laboratory assessments [26, 27]. This setting provides rich and detailed information on both the background level of mood and well-being (tonic levels), as well as the frequency and magnitude of acute fluctuations (phasic variation), and identifies specific periods when these occur (for example, early morning). EMA data offer the opportunity to evaluate hypotheses regarding the dynamic interactions among processes over time—in our case, how different systemic cortisol dynamics could affect reactivity, mood and well-being perception [28, 29].

#### Leeds Sleep Evaluation Questionnaire

During day 5 of each study arm participants are asked to complete the Leeds Sleep Evaluation Questionnaire (LSEQ). This scale comprises ten self-rating 100-mm-line visual analogue questions evaluating four main components: sleep initiation, sleep quality, ease of waking and behaviour following waking. Anonymised data is transferred to the University of Bristol computers. Application of the LSEQ offers consistent and meaningful findings concerning subjectively perceived changes in sleep during psychopharmacological investigations, offering good retest reliability, cross-cultural validity and stability across a range of clinical settings [30–32]. Moreover, it has recently been used to correlate basal diurnal salivary cortisol profiles with sleep quality [33].

#### P1vital Oxford behavioural assessments

Participants undertake a series of emotion-related experimental paradigms, primarily designed to measure biases in emotional processing that are thought to be core components of depression [34]. The P1vital® Oxford Emotional Test Battery (ETB) consists (in our study design) of four paradigms consecutively run during one session which takes place during the fifth day per study arm. The paradigms follow the same order as presented below. The Facial Expression Recognition Task (FERT) assesses the interpretation of facial expressions. Faces of six different basic emotions (happiness, fear, anger, disgust, sadness, surprise) are displayed on the screen and subjects are required to indicate the expression of the face via a button-press. Different intensity levels of each emotion are presented, which increases the ambiguity of the facial expression and the sensitivity of the task. The Emotional Categorisation Task (ECAT) assesses speed to respond to positive and negative self-referent personality descriptors. Sixty personality characteristics selected to be disagreeable or agreeable are presented. The subjects are asked whether they would like or dislike to be referred to as each characteristic. The Faces Dot Probe Task (FDOT) assesses attention to positive versus negative stimuli using a reaction time measure. Two faces are presented vertically on the computer screen and replaced by a pair of dots, to which the subject has to respond by indicating whether the dots are vertically or horizontally aligned. During some trials, one of the two faces presented has an emotional expression (fearful or happy). The reaction time to respond to the dots presented in the same or different location to the face stimuli can be used as a measure of attention to the emotional faces. The stimuli are presented either masked (briefly and replaced by a scrambled face stimulus) or unmasked (subject to conscious awareness). Lastly, the Emotional Recall Task (EREC) is a surprise free recall task to assess the incidental encoding of emotional stimuli. Subjects are asked to recall as many of the words previously presented in the ECAT task as they can. The relative recall of positive versus negative words gives a measure of emotional biases in memory. Contrary to all previous tasks, the latter one is not computerised (subjects write the recalled words on a piece of paper).

Another behavioural test that participants undergo during the fifth day of each study arm is the P1vital® Oxford Emotion Potentiated Startle Test (EPST). EPST is designed to provide an objective measure of response to different emotional stimuli [35]. Subjects are exposed to three consecutive blocks of visual stimuli (= photographs from the International Affective Picture System database with positive, negative or neutral content), while being synchronously exposed to temporally random acoustic stimuli (startle-eliciting pulses through white noise). Startle responses are recorded using electromyography of the orbicularis oculi muscle. Electromyographic data are stored anonymously in the University of Bristol electronic databases.

FERT, ECAT, FDOT, EREC and EPST have been used in previous behavioural and fMRI studies and have been established as models of emotional and cognitive processing sensitive to the effects of neuropsychopharmacological interventions [36]. Moreover, the test-retest reliability of these tasks is good for the purposes of this crossover study, with the exception of FERT where performance of healthy subjects was found improved one week after a baseline test, though the relative effect of specific emotions was unaltered [37]. To overcome this issue and despite the fact that our test-retest period will be longer than a week, we have introduced different facial stimuli per testing session.

